**Figure 1 ztag103-F1:**
[figure not shown]
Diagram of validation phase. Each newborn with blinded cardiovascular status will undergo clinical screening as indicated by current practice and regulations and digital screening using the DI_SOUND algorithm. Gold standard evaluation will be comprehensive echocardiography. Pertinent diagnostics are reported at the bottom.

Cost-effectiveness validation (Aim 3)

Aim 3 will evaluate the potential impact of digital screening on healthcare utilization and costs compared with current standard clinical screening. The target population will consist of newborns at low risk for SHD, with no prior indication for cardiovascular examination, in order to approximate the prevalence of undiagnosed cardiovascular abnormalities in the general newborn population.

For the purpose of this analysis, outcomes will be explicitly defined as follows:

Prevented unnecessary examinations: cases in which (healthy) newborns with a positive result at standard clinical screening but a negative result at digital screening are subsequently confirmed to be free of SHD (i.e. false positives avoided by digital screening).Missed necessary examinations: cases in which newborns (with SHD) with a positive result at standard clinical screening but a negative result at digital screening are subsequently diagnosed with SHD (i.e. false negatives introduced by digital screening).

A decision-analytic modelling framework will be developed to compare digital screening with standard clinical practice. Model inputs will include estimates of SHD prevalence, test performance characteristics (sensitivity and specificity of both screening strategies), and downstream diagnostic pathways. Cost estimates will be derived from national diagnosis-related group reimbursement schedules to reflect healthcare system expenditures associated with confirmatory examinations and missed diagnoses.

To account for parameter uncertainty and variability, a probabilistic sensitivity analysis will be conducted using Monte Carlo simulation. This approach will allow repeated sampling from predefined distributions of key parameters (e.g. prevalence, sensitivity, specificity, and costs) to generate distributions of expected costs and outcomes for each screening strategy. The primary outcome will be the incremental cost-effectiveness of digital screening compared with standard clinical screening, expressed in terms of cost per unnecessary examination avoided and cost per missed SHD case.

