Concordance/discordance pattern between patient-centred comparisons between digital and clinical screening results will be performed using the echocardiography as primary modality of outcome ascertainment (*Figure 1*). False positive will be defined healthy newborns receiving a ‘positive’ screening result using either the clinical (standard or face-to-face auscultation) or the digital approach. Similarly, false negative will be defined newborns with SHD receiving a ‘negative’ screening result using either the clinical (standard or face-to-face auscultation) or the digital approach.

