### Statistic plan

Between-group comparisons for clinical and outcome variables will be performed using independent samples *t*-test, Wilcoxon rank sum test, chi-square analysis, or Fisher's exact test using appropriate variable-specific denominators.

For experimental design Aim 1, limited data are available to build up a reliable power calculation at this stage, but we expect to enrol 600 patients with 2:1 diseased:healthy newborn ratio in this experimental phase. The rationale behind the ratio is due to the higher variability of diseased subjects with respect to the healthy ones.

Specific potential classifiers will be studied in the spectral features, cepstral features, and time-domain features. Dataset will be split into training set, validation set, and test data set. The performance of the classifiers will be evaluated using K-Fold cross-validation. Different folding levels will be tested: 10-fold, 5-fold, and LOOCV, aiming for >95% sensitivity and >90% specificity. The numerosity of the sample we target will allow to estimate the target sensitivity and specificity with sufficient accuracy, in particular with the target numerosity we can estimate a 95% confidence interval of ±2% in the sensitivity estimate and ±4% for the specificity estimate.

Gini importance for Random Forest classifiers will be used as a tool to validate parameters with least predictive contribution. Gini importance can be defined as the probability of making a false classification of a randomly chosen record if it were randomly labelled in the class distribution. During the training of the decision trees of the random forest, each tree is a set of internal nodes and leaves. In the internal node, selected feature is used to make decision of dividing the dataset into two separate splits. Selection of the feature is done with Gini impurity criterion. The feature that brings the highest decrease of Gini impurity is selected for the internal nodes. Even after training, how each feature decreases the impurity can be calculated and accepted as the importance of that feature.

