## Limitation

The most notable limitation is the absence of reliable data to calculate power for the development/training phase. Second, some severe SHD (among others transposition of the great arteries with intact ventricular septum) may have minimal acoustic correlates, and, therefore, our approach may be of limited efficiency for these lesions. Third, clinical screening modality integrates a variety of non-acoustic information, such as general newborn appearance, breathing pattern, femoral pulses, oxygen saturation. It is possible that clinical screening method may outperform digital screening for specific subsets of congenital lesions. Fourth, the frequency response of the digital stethoscope may change significantly between stethoscope models, and this may affect the ability of the classifier to transfer performance to a different model. To mitigate this aspect, we have decided to disable all digital filtering and equalization upon sound acquisition. Development and validation of diagnostic tool in a specific world region may constitute *per se* a limit affecting world-wide generalizability. Lastly, small/premature neonates (<1.5 kg) were not included in the target population of our study by design. This neonatal population routinely undergoes comprehensive cardiovascular evaluation, including echocardiographic screening, which reduces the potential added value of a digital heart sound–based screening tool in this subgroup. They frequently present with clinical and physiological conditions (such as mechanical ventilation, underlying lung disease, haemodynamically significant patent ductus arteriosus, and pulmonary vascular abnormalities) that may introduce substantial acoustic variability and confound heart sound recordings. These factors would limit both the reliability of data acquisition and the generalizability of a classifier intended for the broader neonatal population. Fifth, we are aware that a specificity of 90% may be considered lower than expected for a screening test, however, few consideration should be made to this regard: (i) specificity for current clinical screening modality is reported to be between 95% and 99% with a much lower sensitivity (70–80%) and (ii) our boundary condition is assumed under worst case scenario but we aim for a significantly higher specificity and in the Supplementary material online, *Table S3* of the Online Supplementary Material we are reporting a summary table for diagnostic performance of our classifier under different scenarios showing a sustainable workload for lower specificity compared with optimal specificity (about 80 false-positive newborns every/1000). Finally, given the clinical fragility of preterm infants, we carefully considered the ethical implications of additional handling and sensor application and examination, including potential risks of infection and discomfort.

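### Aim 3's two defined outcomes count only clinical-positive/digital-negative newborns, so the effects in the primary cost-effectiveness ratios are not net and can point the wrong way

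*Protocol article*

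**What the plan says.** The section on cost-effectiveness validation (Aim 3) announces explicit outcome definitions and gives two. The first is "Prevented unnecessary examinations: cases in which (healthy) newborns with a positive result at standard clinical screening but a negative result at digital screening", later confirmed free of SHD. The second is "Missed necessary examinations: cases in which newborns (with SHD) with a positive result at standard clinical screening but a negative result at digital screening", later diagnosed with SHD. The primary Aim 3 outcome is an incremental cost-effectiveness measure, "expressed in terms of cost per unnecessary examination avoided and cost per missed SHD case".

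The same section describes a decision-analytic model: "Model inputs will include estimates of SHD prevalence, test performance characteristics (sensitivity and specificity of both screening strategies), and downstream diagnostic pathways". Monte Carlo simulation is then used "to generate distributions of expected costs and outcomes for each screening strategy". Costs cover confirmatory examinations and missed diagnoses.

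Elsewhere, the Validation phase section says, for Aim 2, that "Concordance/discordance pattern between patient-centred comparisons between digital and clinical screening results will be performed" against echocardiography. The Statistic plan describes the classifier as "aiming for >95% sensitivity and >90% specificity". The Limitation section says that "specificity for current clinical screening modality is reported to be between 95% and 99% with a much lower sensitivity (70–80" (percentages). It adds that 90% specificity is a worst case and that a clearly higher value is the aim.

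**The concern.** Replacing one screening test by another moves newborns in two directions. Among healthy newborns, some clinical false positives disappear and some digital false positives appear. Among newborns with SHD, some clinical detections are lost and some clinical misses are found. Each Aim 3 definition records only the first movement.

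A count of one cell cannot be negative. The plan would therefore credit digital screening with avoided examinations even when it causes more of them overall, and charge it with missed cases even when it detects more overall. The second omission is notable because better detection of SHD is the study's stated purpose, yet Aim 3 has no outcome for a case that digital screening gains.

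There is also a mismatch inside the ratio. If the model's costs include confirmatory examinations for every digital positive while the effect counts only examinations removed, the cost and effect sides describe different sets of newborns.

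**Working it through.** **The plan's own figure.** Aim 3 states no number. The nearest is in the Limitation section: about 80 false positives per 1,000 at the lower specificity compared with the optimal one, taken from a supplementary table that is not shown. With 990 healthy newborns per 1,000:
- as an absolute count at 90% specificity: 990 × 0.10 = 99;
- as an excess over an assumed optimum of 98%: 990 × (0.98 − 0.90) = 79.2;
- as an absolute count at an assumed 92%: 990 × 0.08 = 79.2.

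The documents do not settle which reading is meant, so the figure is not used below.

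**Inputs.**
- Prevalence 1% (Statistic plan, Aim 2 sample size): 990 healthy and 10 with SHD per 1,000.
- Digital specificity 90% (Statistic plan target, taken at its floor).
- Digital sensitivity 95% (same target, at its floor) and 90% (Aim 2 sample size).
- Clinical specificity 95–99% and sensitivity 70–80% (Limitation).

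**Formulas.** Newborns positive on both tests or negative on both cancel between strategies. So:
- net examinations avoided = (healthy, clinical +/digital −) − (healthy, clinical −/digital +) = healthy × (digital specificity − clinical specificity);
- net cases detected = (SHD, clinical −/digital +) − (SHD, clinical +/digital −) = SHD × (digital sensitivity − clinical sensitivity).

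These net values depend only on each test's own accuracy. The single cells also depend on how the tests agree; they are shown assuming independence given true status.

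**Healthy newborns, per 1,000, digital specificity 90%**

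| Clinical specificity | Counted by the plan (avoided) | Not counted (added) | Net avoided |
|---|---|---|---|
| 95% | 990 × 0.05 × 0.90 = 44.6 | 990 × 0.95 × 0.10 = 94.1 | 990 × (0.90 − 0.95) = −49.5 |
| 99% | 990 × 0.01 × 0.90 = 8.9 | 990 × 0.99 × 0.10 = 98.0 | 990 × (0.90 − 0.99) = −89.1 |

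**Newborns with SHD, per 1,000**

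| Digital / clinical sensitivity | Counted (missed) | Not counted (newly found) | Net detected |
|---|---|---|---|
| 95% / 70% | 10 × 0.70 × 0.05 = 0.35 | 10 × 0.30 × 0.95 = 2.85 | +2.5 |
| 95% / 80% | 10 × 0.80 × 0.05 = 0.40 | 10 × 0.20 × 0.95 = 1.90 | +1.5 |
| 90% / 70% | 10 × 0.70 × 0.10 = 0.70 | 10 × 0.30 × 0.90 = 2.70 | +2.0 |
| 90% / 80% | 10 × 0.80 × 0.10 = 0.80 | 10 × 0.20 × 0.90 = 1.80 | +1.0 |

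**Without independence.** Across all possible agreement between the tests, the avoided count in the first table lies between 0 and 49.5 (clinical 95%) or 0 and 9.9 (clinical 99%). The missed count at 95% digital sensitivity lies between 0 and 0.5. The net columns do not change.

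**Digital specificity above the floor.**
- At 95% against clinical 95%, the net is zero, yet the defined count is 990 × 0.05 × 0.95 = 47.0 avoided (independence).
- At an assumed 98% against clinical 95%, the net is 990 × 0.03 = 29.7 avoided, while the defined count is 990 × 0.05 × 0.98 = 48.5 (independence). The direction is right and the benefit is overstated.
- At an assumed 98% against clinical 99%, the net is 990 × (0.98 − 0.99) = −9.9, so the direction is again wrong.

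**The case against.** The strongest reply is that the model already nets. Its listed inputs are the accuracy of both strategies, its outputs are per strategy, and its primary outcome is called incremental. Subtracting one strategy's false positives from the other's gives the net effect directly. The listed inputs could not even produce the single discordant cell without a further assumption about agreement between the tests. On this view the two definitions are only labels.

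Part of this stands. A reader might infer that Aim 3 ignores added false positives and gained cases altogether. The documents do not support that, because both may enter total costs through the model. The omission is certain only for the defined outcomes and for the effects that the ratios name after them. But the definitions are presented as explicit, the ratios take up their terms, and nothing says that they are netted. The result is an inconsistency within one section.

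A reader might also infer that Aim 3 will report the wrong direction for examinations. That does not follow either. The article calls 90% specificity a worst case, and the direction is wrong only if digital specificity falls below clinical specificity. The increase of 49.5–89.1 is the result at the floor, not an expected result.

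Finally, the Aim 2 discordance analysis would make the opposite cell visible. It does not change what Aim 3 defines as its effect. The full protocol and supplementary tables may give more model detail, but the point rests on what the article itself fixes.

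**Conclusion.** The point holds in a limited form: the two Aim 3 outcomes are one-sided, are carried into the primary ratios, and do not fit the two-strategy model beside them.

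- **Examinations:** the direction is wrong whenever digital specificity is below clinical specificity, by 49.5–89.1 additional examinations per 1,000 at the stated floor. Where digital specificity is higher, the direction is right but the benefit is overstated by however many false positives digital screening adds.
- **Cases:** on the article's own figures, an outcome that records only losses conceals a net gain of 1.0–2.5 cases per 1,000.

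These sizes assume 1% prevalence in the low-risk Aim 3 population and digital screening in place of clinical screening, as the definitions imply. The case figures scale directly with prevalence; the examination figures hardly move with it. The net values need no assumption about agreement between the tests.

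**What to change.** Redefine both Aim 3 outcomes as net differences between strategies, using both discordant cells by echocardiographic status:
- **net unnecessary examinations** = (healthy, clinical −/digital +) minus (healthy, clinical +/digital −);
- **net SHD cases detected** = (SHD, clinical −/digital +) minus (SHD, clinical +/digital −), or the same quantity with reversed sign as net cases missed.

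Use these as the effects in the primary incremental ratios, and state that the model costs both discordant cells, so that costs and effects cover the same newborns. Because either net effect may be positive or negative, report incremental cost and both net effects alongside any ratio. The four component counts can stay as descriptive results.

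The cost is minor rewording and a clearer model specification, together with a possibly less favourable result for examinations. No new data are needed: each validation newborn already has clinical screening, digital screening and an echocardiogram.

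### Aim 3 counts newborns who are clinical-positive and digital-negative, but the only accuracy inputs named are each screen's own sensitivity and specificity, which do not determine those counts

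*Protocol article*

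**What the plan says.** All places are in the Protocol article, under Study procedure, Validation phase.

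- **Design.** Both screens are applied to the same child. The Figure 1 caption says: "Each newborn with blinded cardiovascular status will undergo clinical screening as indicated by current practice and regulations and digital screening using the DI_SOUND algorithm".
- **Effect units.** The cost-effectiveness section (Aim 3) defines two. Prevented unnecessary examinations are cases in which "newborns with a positive result at standard clinical screening but a negative result at digital screening are subsequently confirmed to be free of SHD". Missed necessary examinations are newborns "with a positive result at standard clinical screening but a negative result at digital screening are subsequently diagnosed with SHD". The primary Aim 3 outcome is an incremental cost-effectiveness measure "expressed in terms of cost per unnecessary examination avoided and cost per missed SHD case".
- **Model inputs.** These are to include SHD prevalence and "test performance characteristics (sensitivity and specificity of both screening strategies), and downstream diagnostic pathways".
- **Monte Carlo analysis.** It uses "repeated sampling from predefined distributions of key parameters (e.g. prevalence, sensitivity, specificity, and costs" and similar. No concordance, correlation or discordant-cell parameter is named.
- **Paired table.** For Aim 2, the article plans a "Concordance/discordance pattern between patient-centred comparisons between digital and clinical screening results" comparison with echocardiography as reference. The Aim 3 text does not say whether this table feeds the model.

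**The concern.** Each effect unit is a joint probability: positive on one test and negative on the other, in the same newborn, given SHD status. The named accuracy inputs are four marginal probabilities. A joint cell cannot be computed from marginals without a further assumption about dependence. An analyst who holds only the named inputs would most naturally multiply them, which is the assumption of conditional independence.

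That assumption is doubtful among healthy newborns. Clinical screening includes auscultation and the digital screen classifies the same newborn's heart sounds, so a sound that makes one positive may well make the other positive too.

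The two cells are the effect units behind the two primary cost ratios. An error in them passes straight into the ratio, and it does not shrink with more newborns, because it comes from the structure of the model and not from sampling.

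**Working it through.** The article reports no numerical Aim 3 result, so there is no figure to reproduce. The check asks whether the named inputs identify the defined outcomes, and how far apart the answers can be.

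**Inputs from the article**
- Clinical specificity 95–99% and sensitivity 70–80% (Limitation); 97% and 75% are used as mid-range values.
- Digital specificity 90% (lower edge of the Aim 1 target, Statistic plan) and sensitivity 90% (Aim 2 sample size).
- Prevalence 1% (Statistic plan), so 990 healthy newborns per 1000 and about 19 SHD cases in 1900.

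**Assumed input.** Phi, the correlation between the two results within an SHD class, is not in the article. A range is shown.

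**Formula.** Let pC and pD be the probabilities of a positive clinical and a positive digital result within a class. Then

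P(C+, D−) = pC(1 − pD) − phi × √[pC(1 − pC) pD(1 − pD)],

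and the marginals alone restrict it to the interval from max(0, pC − pD) to min(pC, 1 − pD).

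**Healthy newborns** (pC = 0.03, pD = 0.10)
- Bounds: 0 to 0.03, so 0 to 29.7 per 1000 newborns.
- Independence: 990 × 0.03 × 0.90 = 26.7.
- Square-root term: √(0.03 × 0.97 × 0.10 × 0.90) = 0.0512, and 990 × 0.0512 = 50.7.
- phi 0.1: 26.7 − 5.1 = 21.7 (from unrounded values). phi 0.3: 26.7 − 15.2 = 11.5.
- Largest feasible phi: 0.027 / 0.0512 = 0.53.

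Over the article's range of clinical specificity, with digital specificity 90%, prevented examinations per 1000 newborns are:

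| Clinical specificity | phi 0 | phi 0.1 | phi 0.2 | phi 0.3 | Largest feasible phi |
|---|---|---|---|---|---|
| 95% | 44.6 | 38.1 | 31.6 | 25.1 | 0.69 |
| 97% | 26.7 | 21.7 | 16.6 | 11.5 | 0.53 |
| 99% | 8.9 | 6.0 | 3.0 | 0.04 | 0.30 |

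**Would the Monte Carlo analysis reveal this?** With 200,000 draws, Beta distributions on an assumed 1881 healthy newborns and clinical specificity 95%, the 95% interval is 36.2 to 53.8 per 1000 under independence and 18.4 to 32.8 at phi 0.3. The intervals do not overlap. Varying the named parameters does not reach the other answer.

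**SHD cases** (pC = 0.75, pD = 0.90)
- Bounds: 0 to 10 per 100 cases.
- Independence: 0.75 × 0.10 = 7.5 per 100.
- Square-root term: √(0.1875 × 0.09) = 0.130.
- phi 0.1: 6.2. phi 0.3: 3.6. phi −0.1: 7.5 + 1.3 = 8.8.
- Feasible phi: from (0.075 − 0.10)/0.130 = −0.19 to 0.075/0.130 = 0.58.

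**What does not change**
- Total false positives need only the marginals: 990 × 0.03 = 29.7 clinical and 990 × 0.10 = 99.0 digital per 1000, a net difference of −69.3 whatever phi is.
- The uncertainty of a net difference does depend on pairing. With 19 cases, the standard error of the sensitivity difference is √[(0.1875 + 0.09 − 2·cov)/19], where cov = phi × 0.130. That is 12.1 points at phi 0, 10.2 at phi 0.3 and 12.6 at phi −0.1.

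**The case against.** **The article does not commit the error.** It never says that the screens are treated as independent or that their accuracies are sampled separately, and both input lists are open-ended. The Aim 2 paired comparison would supply the missing cells. All of this stands. A reader might infer that the plan assumes conditional independence and that its results will therefore be wrong; the text does not support that. It supports only that the named inputs are insufficient for the named outcomes.

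**This is detail for the full protocol or an economic analysis plan.** That partly stands. How a simulation handles correlated parameters is ordinary plan detail. But the article itself fixes the outcomes as joint cells and specifies the accuracy inputs as marginals. That mismatch is on its face.

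**The direction of dependence is not established.** This stands for SHD cases. A reader might infer that positive dependence inflates both counts. Yet clinical screening also uses saturation and femoral pulses, and the Limitation section says that some severe lesions have minimal acoustic correlates and that clinical screening may do better for certain lesions. Such newborns would be clinical-positive and digital-negative, which pushes phi down and possibly below zero. Among healthy newborns positive dependence remains plausible, though it may be weak: Table 2 counts a physiologic murmur as a negative clinical screen, and the Discussion puts usual screening before discharge, whereas recordings are planned from day 7.

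**Phi is assumed.** True. A value of 0.5 would lie almost at the ceiling for the mid-range healthy case, so the figures relied on here stop at 0.3.

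**Much of Aim 3 is untouched.** Also true: each strategy's expected costs and error totals need only marginals. But the effect units are not defined as net totals.

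**Conclusion.** The point holds as a mismatch between stated inputs and stated outcomes. The two Aim 3 effect units are paired cells, and the only accuracy inputs named do not determine them without an assumption about dependence that the article does not give.

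If only those inputs are used and independence is assumed, prevented unnecessary examinations at clinical specificity 97% and digital specificity 90% would be overstated by a factor of 26.7/21.7 = 1.2 if phi is truly 0.1, or 26.7/11.5 = 2.3 if it is 0.3. For a given incremental cost, the cost per examination avoided would be understated by the same factor. For missed examinations no direction can be claimed: independence gives 7.5 per 100 SHD cases, and the marginals allow 0 to 10.

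These sizes rest on the article's reported or target accuracies and on assumed values of phi. Expected totals per strategy and their net differences stand as planned; only the uncertainty of those differences depends on the pairing.

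**What to change.** In the Aim 3 section:

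1. Name the clinical-by-digital 2×2 table, one for newborns with SHD and one for newborns without, as the accuracy input. State that it comes from the paired comparison already planned for Aim 2.
2. Draw each table jointly in the Monte Carlo analysis, by bootstrapping whole newborns or by Dirichlet draws on the four cells. Compute every Aim 3 outcome, and both strategies' sensitivity and specificity, from the same draw.
3. If Dirichlet draws are used, state a weak prior and check sensitivity to it, because the SHD table will hold only about 19 cases or fewer. At phi 0.3 the clinical-positive, digital-negative cell expects 19 × 0.036 = 0.68 cases. A prior weight of 1 per cell gives a posterior mean of 1.68/23 = 7.3%, about twice the assumed 3.6%; a weight of 0.25 per cell gives 0.93/20 = 4.7%.
4. Where literature values replace a marginal, add a conditional-dependence parameter for each class and vary it over its feasible range, including negative values for SHD.

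**Cost.** A few sentences and a small change in model code; no new data, since both results are recorded for each newborn. The uncertainty for missed cases will be wide, and prevented examinations will probably be fewer than under independence.
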